## Abstract

**Background:**

Osteoporotic fractures are serious consequences of osteoporosis, which is a condition that can be prevented through effective therapeutic strategies, including the use of anti-osteoporotic medications. However, a significant treatment gap exists in elderly patients with osteoporotic fractures. A multicenter study conducted in China reported that only 20% of elderly patients with hip fractures received appropriate pharmacotherapy post-fracture. This lack of treatment resulted in an increased risk of refracture associated with osteoporosis. Pharmacist-led interventions have proven essential in medication management for osteoporosis and related fractures, potentially bridging the treatment gap. Accordingly, a protocol was developed to assess the impact of pharmacist-led interventions on increasing the continuation rates of anti-osteoporotic drugs and reducing the risk of refracture in patients with osteoporotic fracture, compared to no interventions (grant number: YCTJ-2023-15).

**Methods and analysis:**

This study is a single-center, prospective, and randomized controlled trial. The targeted participants in this protocol were patients aged above 50 years who had been diagnosed with osteoporotic fractures in China. Eligible participants were randomized into intervention and control groups in a 1:1 ratio using a dynamic stratified block randomization method. The control group received standard care, and the intervention group received standard care combined with pharmacist-led care. The intervention group received comprehensive pharmacist-led interventions, including pharmaceutical ward rounds and medication reconciliation, refracture risk evaluation, recommendations to physicians, patient education, and counseling. A 2-year follow-up was conducted to evaluate the outcomes between groups through telephone interviews, pharmaceutical clinics, and e-hospital pharmacy practice. The primary outcome is the ongoing treatment rates of anti-osteoporotic drugs. The treatment rates are defined as the ratio of patients who remain on anti-osteoporotic medications at each follow-up visit to the total number of enrolled participants. Secondary outcomes include treatment initiation rates, medication adherence, re-fractures, and use of drugs that increase fall risk, the frequency of bone mineral density (BMD) assessments, the incidence of inappropriate medication use, adverse drug reactions (ADRs), and patient satisfaction with osteoporotic fracture treatment. Refracture rates were evaluated through a 2-year follow-up, while BMD were measured at baseline, 1 year, and 2 years using dual-energy X-ray absorptiometry (DXA). ADRs and the inappropriate use of medication were monitored through self-reports and medication reconciliation. Patient satisfaction were assessed using the Treatment Satisfaction Questionnaire for Medication version II (TSQM-II). Ethical approval was obtained from the Committee of Ethics of the First Affiliated Hospital of Shantou University Medical College (approval number: B-2023-194). The statistical analysis was performed using Statistics Package for the Social Science (SPSS), version 23.0.

**Discussion:**

We hypothesize that analyzing pharmacists-led interventions provide valuable insights into how pharmacists improve treatment outcomes for patients with osteoporotic fractures. This study aims to address the existing knowledge gap regarding the effectiveness of pharmacist-led interventions in improving the management of osteoporotic fractures in China.

## Introduction

1

Osteoporosis (OP) is a systemic disease characterized by reduced bone mass and strength, primarily affecting the elderly population. In China, osteoporosis affects 32% of individuals over the age of 65 years, with women comprising 51.6% of this group (1, 2). Osteoporotic fractures (OFs), also known as fragility fractures, are a prevalent and serious consequence of osteoporosis, significantly affecting the quality of life and elevating the economic burden on both patients and society. The prevalence of OFs in China is predicted to reach 5.99 million by 2050 (3), highlighting the urgent need for effective management strategies.

Effective treatment for osteoporosis, including the use of anti-osteoporotic medications, has been shown to reduce the risk of subsequent fractures by 14–22% (4) and mortality by 19–36% (5) in patients with hip fractures. However, a significant treatment gap persists, particularly among elderly patients with osteoporotic fractures (6). A cohort study has revealed that only 27.7% of women received osteoporosis medications within 12 months after an index fracture, while 72.2% remained untreated (7). A multicenter study in China reported that only 20% of elderly patients with hip fractures received appropriate pharmacotherapy after their fractures, while over 80% remained untreated (8). This significant treatment gap is further worsened by low treatment initiation and adherence rates, which are critical factors in osteoporosis management (9). The risk of drug-associated issues in elderly patients with osteoporosis is aggravated due to multiple prevalent diseases, polypharmacy, and surgical approaches. Elderly patients with osteoporosis are at a higher risk of falls and refractures (10). Polypharmacy may increase this risk of falls and refractures due to the presence of drugs that increase fall risk (11), resulting in the treatment failure for osteoporosis. Therefore, further medication management of polypharmacy is needed for elderly patients with osteoporotic fractures.

Pharmacist-led interventions have been shown to play a crucial role in addressing treatment gaps in osteoporosis (12). A previous study involving 108 patients with hip fractures revealed that pharmacist interventions improved the quality of medication treatment, reduced the use of potentially inappropriate medications, and optimized pharmacotherapy at the time of discharge (13). Pharmacist-driven osteoporosis management has resulted in an increase in the percentage of rural veteran patients who underwent dual-energy X-ray absorptiometry (DXA) screening (14). Overall, pharmacist interventions significantly improved the compliance rates with guidelines for glucocorticoid-included osteoporosis compared to patients who did not receive the intervention (15). A study comparing the impact of pharmacist-led and nurse-led interventions in postmenopausal women with fractures demonstrated a significantly higher increase in the initiation rate of osteoporosis drugs driven by pharmacists compared to nurse-led interventions (16). Only a few studies have investigated the relationship between pharmacist interventions and osteoporotic medication adherence (17–19). However, the impact of pharmacist-led interventions on osteoporosis management, particularly in the context of fracture prevention and treatment adherence, remains underexplored in China. The effectiveness of pharmacist interventions in conventional therapy is still undefined, despite several studies demonstrating a positive correlation between pharmaceutical interventions and osteoporotic treatment.

Given the significant treatment gap and the potential benefits of pharmacist-led interventions, this study aims to evaluate the effectiveness of a comprehensive pharmacist-led intervention model in improving treatment rates of anti-osteoporotic drugs among elderly patients with osteoporotic fractures. This study provides valuable insights into the role of pharmacists in osteoporosis management and contribute to the development of effective strategies for improving patient outcomes in China.

## Materials and methods

2

### Study design

2.1

This protocol follows a single-center, prospective, randomized, and controlled design, in accordance with the Standard Protocol Items: Recommendations for Interventional Trial (SPIRIT) 2013 Statement. The recruitment date was from 1 October 2023 to 30 June 2024. Patient enrollment for the study is ongoing.

### Participants

2.2

Eligible participants were recruited from The First Affiliated Hospital of Shantou University Medical College. The National Osteoporosis Foundation guidelines recommend that medication consideration be given after hip or vertebral fractures in postmenopausal women and men aged 50 years and older (8). The study focused exclusively on patients aged 50 years and older who have been newly diagnosed with osteoporotic fractures, including hip, vertebral, and wrist fractures, according to the International Classification of Diseases, Tenth Revision, Clinical Modification (ICD-10-CM) (20). Therefore, the inclusion criteria are as follows: (1) patients aged 50 and older; (2) those newly diagnosed with an osteoporotic fracture, including hip, vertebral, and wrist fractures.

Exclusion criteria are as follows: (1) Cognitive deficit (cognitive ability to respond and perform the exercises assessed by the Mini-Mental State Examination; MMSE); (2) severe liver insufficiency (Child-Pugh lever C) and severe renal insufficiency (eGFR <30 ml/min/1.73m^2^); (3) use of glucocorticoid drugs within the past 6 months; (4) presence of a malignant tumor or an expected life expectancy of less than 2 years; (5) hospitalization duration of less than 48 h; (6) lack of basic information; (7) patients who died during hospitalization; and (8) unwillingness to participate in this study or refusal to sign the informed consent form.

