### Randomization and allocation

2.4

The patients diagnosed by orthopedists were screened for eligibility based on clinical inclusion criteria. The medical records of those who met the criteria were then forwarded to surgical pharmacists. Patients were randomly assigned to standard care or pharmacist-involved care (1:1 ratio) by team members not involved in clinical pharmacy services, based on whether they received intervention from surgical pharmacists. A dynamic stratified block group randomization method was used to randomly group participants, stratified by sex and age of participants, using R package blockrand (R version 4.0.3).

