### Surgical pharmacist intervention pathway

2.6

The goals of pharmaceutical care involved both orthopedists and patients with osteoporotic fractures. On the one hand, surgical pharmacists provided prescription reviews and consultations with physicians on treatment options for osteoporosis. On the other hand, pharmaceutical care for patients consisted of explaining the importance of diagnosing and treating osteoporosis, providing guidance on the fall risks, and outlining the main precaution related to the use of anti-osteoporotic drugs.

Patients allocated to the intervention group received pharmacist-involved care to identify the effects of pharmaceutical services in OF treatment. On the basis of the standard care, surgical pharmacists, dressed in standard and appropriate professional attire, conducted bedside pharmaceutical consultations individually at three distinct stages: on the first day of admission; within 1 week post-surgery or once the condition is stable; and on the day of discharge. This interaction typically spans a duration of 10–20 min.

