#### Day 1 of admission

2.6.1

A drug reorganization form will be completed to collect medication history, drug allergies, and current medication use, as recorded by the surgical pharmacist through pharmaceutical diagnosis. The bone mineral density (BMD) measurement and exact therapeutic plans are formulated by orthopedists. Consultative reviews are further established by surgical pharmacists, focusing on: (1) the usage and dosage of therapeutic drugs; (2) soluble media; (3) drug contraindication; (4) risks of adverse drug reactions (ADRs); and (5) collaborative drug treatment for chronic disease, including diabetes, hypertension, and hyperlipidemia. Surgical pharmacists will send a new medicine/deprescribe or a change based on the consultative review to orthopedists if indicated. Otherwise, it is necessary for surgical pharmacists to communicate with orthopedists and nurses for medication errors, adjustment in current medicines, and provide medical consultation.

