### Regular follow-up and engagement

2.7

Participants who did not take the medication as scheduled beyond 8 weeks of the expected follow-up period, as well as those who no longer wish to participate in the study, were discontinued from the study.

To address the potential for missing data due to the high dropout rate in the elderly population, we will incorporate an intention-to-treat (ITT) analysis approach. ITT analysis will include all randomized participants in the analysis according to their assigned group, regardless of whether they completed the follow-up or not, which may minimize the bias introduced by missing data and provide a conservative estimate of the treatment of the treatment effect (6).

Participants will be followed up at 1 week, 1 month, 3 months, and then every 3 months thereafter for a total of 24 months. This frequent and structured follow-up schedule is designed to enhance participant retention and ensure comprehensive data collection.

Multiple follow-up methods, including telephone interviews, pharmaceutical clinic visits, and pharmacy practice in e-hospitals, will be used to accommodate different preferences and accessibility of elderly patients.

Trained pharmacists will conduct telephone interviews to gather detailed information on medication use, adverse reactions, falls, and fracture events. Face-to-face consultations at the pharmaceutical clinic will provide personalized medication education and counseling, addressing patient questions and offering the necessary support. For patients unable to visit the clinic, real-time pharmacy practice in e-hospitals via video conferencing or instant messaging will ensure timely information and support.

To ensure comprehensive coverage and maintain data quality, all research staff involved in data collection, including pharmacists and clinic personnel, underwent comprehensive training on the study protocol, data collection methods, and the use of standardized tools. Additionally, we involved family members or caregivers in the follow-up process to provide accurate information on participants’ conditions and medication adherence, ensuring complete and reliable data.

To encourage participant retention, educational materials and personalized support were provided during each follow-up session.

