### Statistical analysis

2.11

The statistical analysis will be along with the intention-to-treat (ITT) principles. The ITT population will include patients who meet the criteria, are randomized, and take at least one dose of drugs after being enrolled (Figures 2, 3).

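### Two exclusion criteria (stay under 48 h, death in hospital) become known only after allocation, so randomised patients can be dropped, against the plan's own all-randomised rule

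*Protocol article*

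**What the plan says.** Section 2.2 (Participants) of the protocol article includes in its exclusion list "5) hospitalization duration of less than 48 h; (6) lack of basic information; (7) patients who died during hospitalization". Criteria 5 and 7 are worded as things that have happened. Criterion 4 in the same list, by contrast, uses an expectation about survival.

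Section 2.4 describes screening followed by assignment: "The patients diagnosed by orthopedists were screened for eligibility based on clinical inclusion criteria". It mentions no wait of 48 h and no wait until discharge.

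Section 2.6 places the pharmacist consultations "on the first day of admission; within 1 week post-surgery or once the condition is stable; and on the day of discharge". Section 2.6.1 gives the day-1 content, beginning with "A drug reorganization form will be completed to collect medication history, drug allergies, and current medication use".

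The analysis population is described three times:

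- Section 2.7: "ITT analysis will include all randomized participants in the analysis according to their assigned group", whether or not follow-up was completed.
- Section 2.8.1: the primary rate has all enrolled participants as its denominator.
- Section 2.11: "The ITT population will include patients who meet the criteria, are randomized, and take at least one dose of drugs after being enrolled".

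**The concern.** An exclusion criterion is harmless when it is settled before allocation. When it is settled afterwards, it removes randomised patients because of what happened to them, and the groups compared are no longer the groups that were randomised. Criteria 5 and 7 are of the second kind if arm-specific care starts on day 1. The section 2.11 definition could carry them into the analysis, because a patient who dies in hospital or leaves at 36 h no longer satisfies the section 2.2 list.

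At stake is the primary comparison of continued treatment rates. A patient who dies in hospital cannot be on drug at any later visit, so taking that patient out of the denominator raises the arm's rate. If the arms lose different numbers, the difference between them shifts. The clause in section 2.11 requiring at least one dose is a separate post-randomisation condition. Deleting it alone would leave this problem in place.

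**Working it through.** **Step 1: order of events.** The moment of randomisation is not stated, so it has to be inferred.

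| Event | Source | When it is known |
|---|---|---|
| Screening, then assignment | 2.4 | no waiting period stated |
| First pharmacist contact, intervention arm only | 2.6, 2.6.1 | day 1 of admission |
| Stay shorter than 48 h (criterion 5) | 2.2 | at discharge or at 48 h |
| Death in hospital (criterion 7) | 2.2 | at the end of the admission |

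Arm-specific care on day 1 requires assignment by day 1. Neither criterion can be settled by then. Criterion 7 is the clearer case, because it is settled only when the admission ends. Randomising later would contradict the day-1 contact.

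**Step 2: the three population statements.** Take a randomised patient who dies in hospital. Sections 2.7 and 2.8.1 keep this patient. Section 2.11, read with section 2.2, removes the patient. The statements cannot all apply.

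**Step 3: the plan's own figure.** Inputs from section 2.10: 50% versus 30%, two-sided alpha 0.05, power 80%, dropout 20%.

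- n = (1.960 + 0.842)² × (0.50×0.50 + 0.30×0.70) / 0.20² = 90.26, rounded up to 91 per group.
- 91 / 0.80 = 113.75, rounded up to 114 per group, 228 in total.

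The stated sample size reproduces and is not in question here.

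**Step 4: effect on an arm's rate.** Let p be the true rate among all randomised, e the fraction removed, and r the rate among those removed. The reported rate is (p − e·r) / (1 − e). The documents give neither e nor r, so the values below are assumptions.

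*All removed are non-users (r = 0; certain for deaths), true rate 30% in both arms:*

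- 5% versus 2% removed: 0.30/0.95 = 31.6% and 0.30/0.98 = 30.6%, a spurious +1.0 point.
- 10% versus 2% removed: 0.30/0.90 = 33.3% and 30.6%, a spurious +2.7 points.
- Equal removal: both rates rise equally, difference 0.

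*Same assumption, with the planned 50% versus 30%:* equal removal of 5% gives 0.50/0.95 = 52.6% and 31.6%, a difference of 21.1 instead of 20 points.

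*Removed patients like the rest of their arm (r = p):* (p − e·p)/(1 − e) = p, so nothing changes.

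*Removed patients all users (r = 1), true rate 30%, 5% versus 2% removed:* (0.30 − 0.05)/0.95 = 26.3% and (0.30 − 0.02)/0.98 = 28.6%, a difference of −2.3 points.

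The last two cases matter for short stays, where r is unknown. The effect may be nil or of either sign.

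**Step 5: effect on power.** If 5% are removed on top of 20% dropout, 114 × 0.95 × 0.80 = 86.6 per arm remain. Power by the pooled-variance formula is 77.1%, against 79.1% at 91 per arm. This is a minor loss.

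**The case against.** The strongest reply is that no sentence says randomised patients will be deleted under criterion 5 or 7. Section 2.7 and the section 2.8.1 denominator both point to keeping them. Section 2.4 uses wording close to that of section 2.11 for screening done before assignment, so section 2.11 might mean only that. This stands in part: removal is permitted by the text and is not an explicit rule. It does not clear the plan, because death in hospital cannot be screened for before day-1 care, whichever way section 2.11 is read.

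A reader might go further and infer that nearly everyone removed would have failed on the primary outcome, so that both rates must be inflated. The documents support this for deaths only. Patients discharged within 48 h are alive and can be followed, wrist fractures are eligible, and nothing indicates that these patients would be off drug.

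A reader might also infer large distortions, for example by supposing 10% removed or removal from one arm only. No rate in the documents supports either. Section 2.2 already excludes patients with malignancy, short life expectancy or severe liver or kidney insufficiency, which should lower in-hospital mortality. The criteria also apply to both arms.

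Nor do the documents show that the intervention alters early discharge. Consultations last 10 to 20 minutes, orthopaedists manage both arms, and the discharge consultation is set by the discharge day. Unequal removal is possible but not demonstrated.

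**Conclusion.** The point holds as a conflict over the analysis population. As worded, criteria 5 and 7 can be applied only after allocation. With section 2.11 they permit post-randomisation exclusions that sections 2.7 and 2.8.1 rule out. This rests on inferring from the day-1 contact that allocation has occurred by then; nothing in the article suggests a later time.

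The size cannot be determined from the documents and is probably small. Unequal removal of 5% versus 2%, all non-users, would produce about 1 point of spurious difference under a true 30% in both arms; equal removal would produce none. For deaths the direction within an arm is certain (upward); for short stays it is unknown. The text does not support the stronger conclusion that the treatment comparison is necessarily inflated.

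**What to change.** 1. **Section 2.2:** stop using criteria 5 and 7 to remove patients after randomisation. Apply only what is known before allocation.
2. **Section 2.11:** bring the ITT definition into line with sections 2.7 and 2.8.1, so that every randomised patient is analysed in the assigned arm.
3. **Early discharges:** follow them and count the treatment status observed, using the planned missing-data rule where it is unknown. Coding them all as not on treatment would misclassify living patients who can be followed.
4. **In-hospital deaths:** count them as not on treatment. State this explicitly, because section 2.8.1 assesses the outcome after discharge and these patients never reach that point.

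**Cost:** wording in 2.2 and 2.11, follow-up of what are probably few early discharges, and possibly slightly lower reported rates. Section 2.1 gives recruitment dates from October 2023 to June 2024 and calls enrolment ongoing, so the eligibility wording can help only patients not yet enrolled. The analysis-set correction covers everyone randomised, provided the data of any patient already set aside are kept or recovered.

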### Withdrawal criteria

2.3

Patients can voluntarily withdraw from this clinical trial at any time. Additionally, patients were required to withdraw from the trial if they experience any of the following conditions: (1) Serious adverse events (AEs) occurring at any point during the entire trial process; (2) Inability to continue participating in clinical examinations and follow-up due to unexpected reasons.

